### Sample size

The sample size calculation is based on the primary endpoint, rectal preservation, defined as the absence of the need for completion TME due to discontinuation criteria or local recurrence and rescue to TME. The assumptions are based on data from our group: in T1 tumors, the sm3 rate is 35–40%, with 5–10% of patients presenting adverse pathological factors; in the TAUTEM trial (T2–T3ab), the pCR rate was 44%, therefore a pCR > 55% is expected in T1 cases [22]. Assuming a two-sided test for difference in proportions with α = 0.05 and β = 0.20 (power 80%), 53 patients per group are required to detect as significant a difference between p₁ = 0.60 (TEM) and p₂ = 0.85 (CRT–TEM). Considering a 10% dropout rate, the total sample size will be 106 patients.

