There are several classifications used to assess submucosal invasion (Haggitt, Kikuchi, Ueno, Kudo, and Kitajima); however, they present limitations and relevant variability that may influence clinical decision-making. Therefore, our group has proposed the Taulí-pT1 classification, which quantifies tumor invasion according to the area of residual healthy submucosa in the specimen, using a uniform methodology based on a percentage derived from a constant reference point [11]. This classification shows excellent correlation with Kitajima’s and very good correlation with Kudo’s system. Its only requirement for applicability is the presence of the muscularis propria in the specimen. Recently, we have published its validation through interobserver concordance analysis [13].

Recent studies with large cohorts and long-term follow-up (although with retrospective designs) have reopened the debate on local surgery for pT1N0M0 rectal cancer. Leijtens et al. [14] reported, in a series of 150 patients with a median follow-up of 58.9 months, a local recurrence (LR) rate of 22.7% and an overall survival (OS) of 82%; even when stratifying tumors without adverse prognostic features, LR rates exceed 20%. Recently, we have published our long-term follow-up cohort, with a median follow-up of 91 months (IQR: 84), 17 patients (16.3%) developed LR and 14 (13.5%) developed distant recurrence. Five-year rectal cancer–specific and overall survival rates were 95% and 74%, respectively. Among the 88 patients without histopathological or surgical high-risk factors, 13 (14.8%) experienced LR and 9 (10.2%) distant recurrence [15].

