### Study variables

#### Primary variable (endpoint)

Difference in rectal preservation rate between CRT–TEM and TEM at 3 years after surgery. The database will be locked after all randomized patients have completed a minimum of 3 years of follow-up for the primary endpoint assessment.

Rectal preservation failure is defined as any completion TME due to protocol discontinuation criteria (e.g., adverse pathology or inadequate response) and/or any salvage TME performed for local recurrence during follow-up.

Local recurrence will be considered a rectal preservation failure irrespective of the subsequent management strategy (including cases treated without TME). Any TME performed for any reason during the 3-year follow-up (including postoperative complications, patient preference, or conversion to abdominal surgery resulting in TME) will be classified as rectal preservation failure. A temporary diverting stoma does not constitute rectal preservation failure; however, a permanent stoma at 3 years (even in the absence of TME) will be classified as rectal preservation failure. Death before 3 years and losses to follow-up will be handled under the ITT framework; in the primary analysis, patients without documented rectal preservation status at 3 years will be conservatively counted as failures, with sensitivity analyses using alternative assumptions. Patients who do not undergo TME for any reason but have persistent/uncontrolled primary disease will be counted as rectal preservation (rectum in situ) but will be recorded as local failure and as non–disease-free (DFS event).

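### The planning rates 0.60 and 0.85 do not cover the primary endpoint as it is scored, and counting the planned 10% dropout as failures takes the power from the stated 80% to about 70%

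*Protocol article*

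**What the plan says.** The Sample size section describes the endpoint as freedom from completion TME under the discontinuation criteria and from local recurrence with rescue TME. The basis it gives is the group's own data: "in T1 tumors, the sm3 rate is 35–40%, with 5–10% of patients presenting adverse pathological factors". For the experimental arm it cites a pCR of 44% in the earlier T2–T3ab trial and concludes "therefore a pCR > 55% is expected in T1 cases". It then sets 0.60 for TEM and 0.85 for CRT–TEM, two-sided α 0.05 and power 80%, states that "53 patients per group are required", and ends: "Considering a 10% dropout rate, the total sample size will be 106 patients".

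Other sections determine what counts as a failure:

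- **Criteria for exiting the study protocol.** Completion TME is indicated for adverse factors, sm3, missing muscularis propria, a margin below 1 mm, or a stage above pT1/ypT1. Upstaging on week-9 MRI leads to TME before any local excision.
- **Primary variable (endpoint).** "Local recurrence will be considered a rectal preservation failure irrespective of the subsequent management strategy". In the primary ITT analysis, patients without documented status at 3 years are counted as failures.

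The Introduction supplies recurrence figures. After local excision alone: "Among the 88 patients without histopathological or surgical high-risk factors, 13 (14.8%) experienced LR". After CRT–TEM in T2–T3ab the 5-year figure is 7.4%.

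**The concern.** The Sample size section names local recurrence as part of the endpoint but lists no recurrence rate among its inputs. The inputs it does list appear to account for the whole of the 40% failure rate in the TEM arm. For CRT–TEM it gives a lower bound on pCR but no failure rate for patients without pCR, no recurrence rate and no rate of week-9 exits, so 0.85 cannot be traced. Dropout is handled as a loss of patients, whereas the endpoint rule keeps those patients and scores them as failures. The stated 80% power therefore belongs to an outcome narrower than the one that will be analysed. Readers and the oversight body would be relying on a figure that holds for some combinations of the article's own inputs and not for others.

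**Working it through.** **1. The plan's own figure.** Unpooled normal approximation, (1.960 + 0.842)² = 7.849:

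n = 7.849 × (0.60×0.40 + 0.85×0.15) / 0.25² = 7.849 × 0.3675 / 0.0625 = 46.15, so 47 per arm. Then 47 / 0.90 = 52.2, so 53 per arm and 106 in total. The figure reproduces, with the 10% dropout already inside 53. Exact power of the two-sided Pearson test at 53 per arm, by full enumeration, is 84%.

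**2. TEM rate.** 1 − 0.35 − 0.05 = 0.60, and 1 − 0.40 = 0.60 if adverse cases lie within sm3 at the top of its range. Neither leaves room for recurrence. If all adverse cases lie within sm3 at 35%, preservation before recurrence is 0.65, and 0.60 allows a recurrence rate of 1 − 0.60/0.65 = 7.7%, about 8%. The article gives no rate for upstaging or close margins.

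**3. CRT–TEM rate.** Assumption, not in the article: patients without pCR meet the TME triggers at the untreated rate *c*. Then p2 = (1 − (1 − pCR) × c) × (1 − LR). With c = 0.40 and pCR 55%:

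- no LR: 1 − 0.45×0.40 = 0.82
- LR 7.4%: 0.82 × 0.926 = 0.76

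The pCR that 0.85 requires at c = 0.40:

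- no LR: 1 − 0.15/0.40 = 62.5%
- LR 7.4%: 1 − (1 − 0.85/0.926)/0.40 = 79.5%, about 80%

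**4. Power over the article's inputs.** p1 = (1 − c)(1 − LR₁), with LR either absent in both arms or 14.8% (TEM) and 7.4% (CRT–TEM). Exact Pearson power, 53 per arm:

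| c | pCR | LR | p1 v p2 | Power |
|---|---|---|---|---|
| 0.40 | 55% | none | 0.60 v 0.82 | 72% |
| 0.40 | 55% | 14.8 / 7.4% | 0.51 v 0.76 | 78% |
| 0.50 | 55% | 14.8 / 7.4% | 0.43 v 0.72 | 87% |
| 0.40 | 60% | none | 0.60 v 0.84 | 81% |
| 0.40 | 60% | 14.8 / 7.4% | 0.51 v 0.78 | 84% |

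At c = 0.35 (complete overlap), pCR 55% and both LR figures, 0.55 v 0.78 gives about 70%. Lowering only the TEM rate (0.51 v 0.85) gives 97%.

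**5. Dropout scored as failure.** Assume 10% in each arm end without documented status, unrelated to outcome. The number analysed stays at 53 and the rates shrink:

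- 0.60 × 0.90 = 0.54
- 0.85 × 0.90 = 0.765

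The difference falls from 0.25 to 0.225. Exact power at 53 per arm is 70%. This step accepts the plan's 0.60 and 0.85 and uses none of the assumptions in steps 2 to 4.

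**The case against.** Several points on the other side stand.

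- **The pCR is a floor.** A reader might infer that 0.85 needs a higher pCR than the plan assumes. The article does not support that: above 55% allows 62.5%, and at c = 0.40 a pCR of 60% is enough to bring power above 80% with or without recurrence.
- **The failure rate without pCR is borrowed.** Partial response could lower it, and poor regression alone does not mandate TME.
- **The cited recurrence rates fit loosely.** The 14.8% comes from a cohort with a median follow-up of 91 months, and the 7.4% is a 5-year figure in more advanced tumours; the endpoint is at 3 years. In the first cohort 17 recurrences are 16.3%, so about 104 patients, of whom 88 were without high-risk factors. About 15% were thus high-risk, which sits poorly with an sm3 rate of 35–40% unless sm3 was handled differently there. Applying 14.8% after removing sm3 cases may count some risk twice.
- **The direction is not fixed.** It is tempting to conclude that the trial is underpowered. Adding recurrence to the CRT–TEM arm alone would suggest so, but that is not a consistent correction, and correcting the TEM rate alone raises power.
- **A condensed article need not show a full build-up.** This is fair as far as a missing derivation goes. It does not answer the point that the section names its endpoint and its basis, and the basis leaves out events that the same endpoint counts.

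None of this touches the dropout step, which needs only the plan's two rates, its 10% and its own scoring rule.

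**Conclusion.** The point holds in a limited form. The arithmetic leading to 106 is correct. The defect lies in what 0.60 and 0.85 represent. The listed inputs use up the TEM failure rate, or leave room for at most about 8% recurrence, before upstaging, margins and undocumented status. The 0.85 is not derived; with the cited 7.4% recurrence and the untreated 40% trigger rate it would need a pCR of about 80%.

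On the component model the stated power is neither confirmed nor refuted. For trigger rates of 40–50% it runs from about 72% to 87% at a pCR of 55%, and is 81% or more at 60%. The firm result is the dropout one: under the primary scoring rule, 10% undocumented status in each arm gives 0.54 v 0.765 and power of about 70%, against 80% stated. This assumes that the loss is equal between arms, unrelated to outcome, and not already included in 0.60 and 0.85; the section applies it separately, which supports that reading. The documents do not support saying that the sample size was miscalculated or that the trial is certainly underpowered.

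**What to change.** In the Sample size section, define p1 and p2 on the primary endpoint as it will be scored. List for each arm the assumed contribution of:

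- completion TME for sm3, other adverse pathology, margins and stage above pT1/ypT1
- week-9 exits (CRT–TEM only)
- local recurrence by 3 years
- deaths and losses counted as failures

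State the pCR used and the failure rate assumed without pCR. Then report the power that 106 patients give over the resulting range, with dropout entered through the rates and not through n. Leave the sample size unchanged.

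The cost is a rewritten paragraph and a small table. The drawback is that the stated power becomes a range that may include values below 80%.

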### Randomization

Patients who meet all inclusion criteria, none of the exclusion criteria, and have signed the informed consent form will be randomized. Allocation to the CRT–TEM or TEM group will be performed in a 1:1 ratio using a computer-generated randomization sequence implemented in the electronic Case Report Form (eCRF) centralized by the Contract Research Organization (CRO). The system will automatically assign treatment once eligibility criteria are confirmed.

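### The stated 80% power does not hold under the protocol's own primary analysis: with the planned 10% dropout scored as failure, 53 per group gives about 69–70%

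*Protocol article*

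**What the plan says.** Four statements in the protocol article bear on this point.

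- **Sample size, test and rates.** The section reads "Assuming a two-sided test for difference in proportions with α = 0.05", with β = 0.20, and rates of 0.60 for TEM and 0.85 for CRT–TEM. It continues that "53 patients per group are required to detect as significant a difference" and closes with "Considering a 10% dropout rate, the total sample size will be 106 patients". Allocation is 1:1 (Randomization).
- **Sample size, endpoint.** The endpoint used for sizing has two kinds of failure: completion TME under the discontinuation criteria, and local recurrence with rescue TME.
- **Primary variable (endpoint).** Deaths before 3 years and losses to follow-up are to be handled under an ITT framework, and "in the primary analysis, patients without documented rectal preservation status at 3 years will be conservatively counted as failures". Sensitivity analyses under other assumptions are planned. This section also counts as failures any TME for any reason, local recurrence managed without TME, and a permanent stoma at 3 years.
- **Statistical analysis.** The principal analysis is ITT and includes all randomised patients.

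**The concern.** Dividing a sample size by one minus the dropout rate is right when dropouts leave the analysis: enough extra patients are enrolled that the remainder still reach the required number. Here dropouts do not leave. They stay in the denominator and count as failures, which multiplies the preservation rate in each arm by one minus the missing fraction. Both rates fall and so does the difference between them. The 25-point contrast used for sizing is then larger than the contrast that the primary analysis would show on the protocol's own dropout figure.

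At stake is the chance of missing a true effect of the planned size. The protocol puts it at 20%. Under its own missing-data rule and its own 10% dropout it is about 30%.

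**Working it through.** **Inputs.** p₁ = 0.60, p₂ = 0.85, two-sided α = 0.05, power 80%, 53 per group, 10% dropout (all from Sample size); missing status counted as failure (Primary variable); all randomised patients analysed (Statistical analysis). z(0.975) = 1.960 and z(0.80) = 0.842, so (1.960 + 0.842)² = 7.849.

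**Step 1: reproduce the plan's figure.** With unpooled variance,

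n = 7.849 × (0.60 × 0.40 + 0.85 × 0.15) / 0.25² = 7.849 × 0.3675 / 0.0625 = 46.15, so 47 per group.

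47 / 0.90 = 52.2, so 53 per group and 106 in total. This matches exactly with the 10% allowance included. Other formulas give a bare requirement of 48 (arcsine), 49 (pooled null variance) or 57 (continuity-corrected).

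**Step 2: power if dropouts were excluded.** 53 × 0.90 = 47.7, so about 48 evaluable per group. The normal-approximation power is Φ(u), with

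u = [(p₂ − p₁)√n − 1.960 × √(2p̄(1 − p̄))] / √(p₁(1 − p₁) + p₂(1 − p₂)), where p̄ is the mean of the two rates.

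For n = 48 this gives 79.3%; exact enumeration of the chi-square test gives 80.4%. The promise of 80% is kept for that analysis.

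**Step 3: power under the stated rule.** Let d be the fraction missing, equal in both arms and independent of outcome. The analysed rates are 0.60(1 − d) and 0.85(1 − d). For d = 0.10 they are 0.54 and 0.765, a difference of 0.225, with p̄ = 0.6525:

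u = [0.225 × √53 − 1.960 × √(2 × 0.6525 × 0.3475)] / √(0.54 × 0.46 + 0.765 × 0.235) = 0.486, and Φ(0.486) = 68.7%.

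| Missing, scored as failure | Rates | Power at 53 per group, normal | Exact chi-square |
|---|---|---|---|
| 0% | 0.60 vs 0.85 | 83.2% | 84.5% |
| 5% | 0.57 vs 0.8075 | 75.9% | 77.1% |
| 10% | 0.54 vs 0.765 | 68.7% | 70.0% |

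**Step 4: size needed.** For 0.54 versus 0.765, the pooled formula gives 70 per group; by the exact chi-square calculation, 68 per group reaches 80%. A second inflation of 53 by 1/0.90, to 59 per group, would give only 73.4% (normal), because it does not address the shrunken difference.

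**Step 5: deaths, as an assumption only.** The Introduction says of the group's earlier pT1 cohort: "Five-year rectal cancer–specific and overall survival rates were 95% and 74%, respectively". Assuming a constant hazard, 3-year mortality would be 1 − 0.74^(3/5) = 16.5%. If every such death were scored as a failure, independently of earlier failure and with no other missing data, the rates would be 0.501 versus 0.710. Power at 53 per group would then be 59.6% (normal) or 60.8% (exact).

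**The case against.** A reader might infer from 2 × 53 = 106 that nothing was added for dropout. The documents do not support that. The bare requirement by the usual formulas without continuity correction is below 53, and 47 / 0.90 rounds up to exactly 53. The authors' formula cannot be proven, but the allowance is probably there. What remains in the Sample size section is loose wording: the inflated number is presented as the required one.

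It is also tempting to state the risk of a false-negative result as 30–45%. The upper part of that range needs deaths to count as failures and needs an assumed mortality. The protocol names deaths beside losses but does not say whether a patient who died with a documented intact rectum lacks a 3-year status. The 74% survival comes from an earlier cohort, whereas this trial requires ASA III or lower and excludes patients who cannot have chemotherapy or radiotherapy. Some deaths will follow a recurrence or TME already counted as a failure and would dilute nothing further. The 10% dropout may also already include deaths.

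Unequal loss between the arms could bias the comparison in either direction, so the rule is not conservative in every case. But the protocol gives no loss rates by arm and already plans sensitivity analyses for missing data, so no figure is attached to that here.

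Finally, low missingness does little harm: at 2–3% missing, exact power is still 81.5% to 80.0%. That is correct, but the protocol's planning figure is 10%. None of these objections removes the mismatch at that figure.

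**Conclusion.** Wrong as written. The claim of 80% power at 53 per group with 10% dropout does not describe the primary analysis that the same document specifies. Under that analysis power is about 69–70% at 10% missing and about 76–77% at 5%. The claim would be right for an analysis that excludes dropouts (79–80%).

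The result rests on three assumptions: missingness is equal in both arms, it is independent of outcome, and 0.60 and 0.85 do not already allow for missing-as-failure. The third is supported by the endpoint wording in the Sample size section, which mentions only TME for discontinuation criteria or recurrence. The figure of about 60% with deaths scored as failures illustrates one assumption and is not an estimate for this trial.

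**What to change.** 1. In Sample size, say that 53 per group already includes the 10% allowance, if the sponsor confirms this, and give the bare requirement and the formula.
2. Restate the power under the missing-as-failure rule: about 83–84% with complete follow-up, and about 69–70% with 10% scored as failures. Either accept the lower figure openly, or note that 80% would need about 68–70 per group.
3. In Primary variable, state whether a death before 3 years with a documented intact rectum counts as a failure.
4. Use one endpoint definition in both sections. The sizing definition omits the failures from missing status, permanent stoma, TME for other reasons, and recurrence managed without TME. Say whether 0.60 and 0.85 allow for them.

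These are wording changes that need no new data; the cost is a less favourable stated power. Enrolling more patients would be a separate decision with real cost. An estimate that censors losses, or treats death as a competing event, could be added to the sensitivity analyses already planned. Replacing the primary analysis is optional and this point does not require it: censoring brings its own assumption of non-informative loss, and no power calculation for that alternative is given here.

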### Interim analysis and stopping rules

Given the superiority design, an interim analysis will be conducted approximately halfway through recruitment (after ~ 50% of patients have been enrolled). Early stopping for benefit will be considered using conservative statistical boundaries with appropriate alpha-spending, and the final significance threshold will be adjusted accordingly. Interim results will be reviewed by an independent oversight body, which will provide a recommendation to the steering committee regarding trial continuation, modification, or early termination.

### Study monitoring

Study monitoring will be performed by the Contract Research Organization (CRO). Contracting of the SCReN (Spanish Clinical Research Network) platform, supported by a grant from the Instituto de Salud Carlos III (ISCIII), will also include pharmacovigilance activities and data management.

### Statistical analysis

The principal analysis, from which the main study conclusions will be derived, will follow the intention-to-treat (ITT) approach, including all randomized patients. A per-protocol (PP) analysis will also be conducted, including patients from both groups who do not meet withdrawal criteria and who complete the study protocol. Losses to follow-up and their potential impact on outcomes will be analyzed. Pre-specified sensitivity analyses will assess the impact of missing primary endpoint data.

Quantitative variables will be described using mean and standard deviation or, when appropriate (based on the Kolmogorov–Smirnov or Shapiro–Wilk normality tests), median, interquartile range, and range. Categorical variables will be summarized as absolute numbers and percentages.

Comparisons between groups for quantitative variables will be performed using the Student’s t-test (when assumptions of normality and homoscedasticity are met); otherwise, the Mann–Whitney U test will be applied. Categorical variables will be compared using Pearson’s χ^2^ test or Fisher’s exact test, as appropriate.

Survival analyses (local recurrence, distant recurrence, and mortality) will be performed using Kaplan–Meier estimates and compared with the log-rank test.

In addition, an exploratory DFS analysis will be performed stratifying patients according to adverse histopathologic features identified in the local excision (TEM) specimen (e.g., lymphovascular invasion, poor differentiation, tumor budding, and depth of submucosal invasion), and results will be interpreted as hypothesis-generating due to limited power for subgroup analyses.

Statistical significance will be set at *p* < 0.05. When applicable, results will be presented with their 95% confidence intervals (95% CI).

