### Criteria for exiting the study protocol

The study protocol will be discontinued and patients will proceed to standard radical surgery with TME in the following pre-excision situations: (i) local excision is not performed using standard transanal endoscopic surgery techniques (TEM, TEO, or TAMIS) or requires conversion to abdominal surgery; or (ii) at week 9 after completion of neoadjuvant therapy, pelvic MRI restaging shows ≥ cT2 and/or cN1 (any T) [41].

Patients who do not complete neoadjuvant therapy due to toxicity, intolerance, or personal decision, and patients with an incomplete clinical response at week 9 without MRI upstaging, will still proceed to local excision (TEM/TEO/TAMIS) as per protocol; treatment modifications and response category will be recorded for secondary analyses.

Following the pathological report of the local excision specimen, the protocol will be terminated and completion TME will be indicated if any of the following are present: adverse prognostic factors (grade G3, venous, lymphatic, or perineural invasion, or tumor budding); absence of the muscularis propria layer preventing evaluation of submucosal invasion; surgical margin (lateral or deep) < 1 mm; submucosal invasion classified as sm3 according to the Taulí-pT1 classification; or pathological stage higher than pT1 or ypT1.

Absence of pathological response to CRT (Bouzourene GR4–GR5 or Dworak GR0–GR1) alone, in the setting of a pT1/ypT1 lesion with clear margins and no adverse features, will not mandate completion TME and patients will continue standard surveillance. Completion TME will be performed within 4–6 weeks according to institutional guidelines and protocols.

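### The per-protocol set, on its natural reading, drops patients who exit the protocol to TME, which the plan counts as endpoint failure, so this secondary comparison selects on the outcome

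*Protocol article*

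**What the plan says.** Three parts of the protocol article have to be read together.

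- **Analysis sets (Statistical analysis).** "The principal analysis, from which the main study conclusions will be derived, will follow the intention-to-treat (ITT) approach", in all randomized patients. A per-protocol analysis is added, "including patients from both groups who do not meet withdrawal criteria and who complete the study protocol". It is given no stated role in the conclusions.
- **Exit rules (Criteria for exiting the study protocol).** Before excision: "The study protocol will be discontinued and patients will proceed to standard radical surgery with TME" if standard transanal excision is not performed or is converted, or if the week-9 MRI shows upstaging. After excision: "the protocol will be terminated and completion TME will be indicated if any of the following are present". The list covers adverse histology, missing muscularis propria, a margin under 1 mm, stage above pT1/ypT1, and "submucosal invasion classified as sm3 according to the Taulí-pT1 classification".
- **Endpoint (Primary variable).** "Rectal preservation failure is defined as any completion TME due to protocol discontinuation criteria" and/or salvage TME for local recurrence. The section then widens this: "Any TME performed for any reason during the 3-year follow-up" is a failure, and so is local recurrence however it is managed.

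The Sample size section expects sm3 in 35–40% of T1 tumors and adverse pathological factors in 5–10%. It plans on 60% preservation with TEM and 85% with CRT–TEM.

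**The concern.** A per-protocol set is meant to show the effect in patients who received what they were allocated. Here a patient who meets an exit criterion and goes on to TME has done what the protocol requires, yet the wording removes that patient. The removal is triggered by the step that produces the endpoint failure, so the set is chosen after randomization on the outcome itself.

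The loss is also unequal by design. The Discussion says the trial tests whether CRT–TEM avoids completion TME triggered by adverse pathology. Dropping those patients removes that component of benefit from the comparison, and mostly from the TEM arm. One criterion, week-9 restaging, can apply only in the CRT–TEM arm.

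At stake is a reported secondary analysis that could show a much smaller effect, or one in the other direction, when the treatment works as planned. Readers often take such a gap between ITT and per-protocol results as a sign of fragility.

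**Working it through.** **1. The plan's own figure.** Inputs from the Sample size section: p₁ = 0.60, p₂ = 0.85, two-sided α = 0.05, power 80%, 10% dropout. The unpooled formula gives n = (1.960 + 0.842)² × (0.60×0.40 + 0.85×0.15) / 0.25² = 46.15, so 47 per group. Then 47/0.9 = 52.2, so 53 per group and 106 in total. The stated size reproduces with dropout inside the 53. Power for 60% v 85% at 53 per group is 83%.

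**2. Formula for the per-protocol set.** Let f be the failure rate in an arm and e the share of the arm that exits, all of them failures (e ≤ f). If only exits are removed:

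per-protocol preservation = (1 − f) / (1 − e).

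Planned failure rates are f = 0.40 (TEM) and f = 0.15 (CRT–TEM).

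**3. TEM arm.** Take e = 0.35, the lower sm3 rate in the document. That removes 0.35 × 53 = 18.6 patients, which is 0.35/0.40 = 87.5% of the planned failures. Per-protocol preservation is 0.60/0.65 = 92.3%. At the upper sm3 rate, e = 0.40, it is 0.60/0.60 = 100%.

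**4. CRT–TEM arm.** The document does not say what share of failures are exits, so the whole range is shown, with TEM exits held at 35%.

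| CRT–TEM exits, share of arm | TEM | CRT–TEM | Difference |
|---|---|---|---|
| 0% (no failure is an exit) | 92.3% | 85.0% | −7.3 |
| 7.5% (half of failures) | 92.3% | 91.9% | −0.4 |
| 11.25% (three quarters) | 92.3% | 95.8% | +3.5 |
| 15% (all failures) | 92.3% | 100% | +7.7 |

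The ITT difference is +25 points in every row.

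**5. Sensitivity to the 35%.** Assume instead that the same share of failures are exits in both arms.

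| Share of failures that are exits | TEM | CRT–TEM | Difference | Power on the remaining patients |
|---|---|---|---|---|
| 50% | 75.0% | 91.9% | +16.9 | 59% |
| 75% | 85.7% | 95.8% | +10.1 | 38% |
| 90% | 93.8% | 98.3% | +4.5 | 20% |
| 100% | 100% | 100% | 0 | – |

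The first two rows imply TEM exits of 20% and 30%, below the document's own sm3 rate.

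**6. The bias can also create a difference.** Suppose ITT preservation is 61.75% in both arms, with exits of 35% (TEM) and 10% (CRT–TEM). Per-protocol preservation is 0.6175/0.65 = 95.0% against 0.6175/0.90 = 68.6%. These exit rates are chosen only to illustrate the mechanism.

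**The case against.** The strongest reply is that nothing depends on this analysis. The trial is a superiority trial, ITT governs the conclusions, and the article does not ask the per-protocol result to confirm anything. That stands. A reader might infer that the flaw weakens the main result; the document does not support this, since no primary estimate, test or sample size changes.

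Second, withdrawal criteria might mean something else, set out in a fuller protocol or analysis plan. Equating them with the exit criteria is an inference. It remains the natural reading: the article gives no other patient-level criteria, and it describes the protocol of these patients as discontinued or terminated, so they do not plainly complete it either.

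Third, the overlap is not exact. Local recurrence, permanent stoma, and death or missing status counted as failure are not exits. A patient who meets a criterion but has no TME could count as preserved. This stands, and it is why the result is a range.

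Three stronger readings should be resisted:

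- **A per-protocol result of about 85% v 93% with some 20% power.** A reader might reach it by taking the article's 14.8% local recurrence in low-risk T1 patients against 7.4% after CRT–TEM, with 40–50% TEM exits. The first rate has a median follow-up of 91 months; the second is a 5-year rate in T2–T3ab disease. The endpoint here is at 3 years in cT1. Those inputs also imply TEM preservation under ITT of 0.60 × 0.852 = 51% down to 0.50 × 0.852 = 43%, not the planned 60%.
- **That this scenario contradicts the ITT benefit.** It still favors CRT–TEM. In the working above, reversal occurs only when few CRT–TEM failures are exits.
- **That at most 15% of CRT–TEM patients would be excluded.** That limits only exclusions among failures. Patients who stop neoadjuvant therapy early still proceed to excision and might be left out as not completing the protocol, without being failures.

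**Conclusion.** The point holds as a defect in a secondary analysis and should be fixed. On the natural reading, the stated per-protocol rule selects on the primary outcome and does so differently by arm. With the ITT effect exactly at 60% v 85%, the per-protocol difference lies between −7.3 and +7.7 points instead of +25.

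That range rests on four assumptions: the withdrawal criteria are the exit criteria; 35% of TEM patients exit and all are failures; only exits are removed; and the share of CRT–TEM failures that are exits may be anything from none to all. If preserved CRT–TEM patients are also dropped for incomplete neoadjuvant therapy, the lower end could fall further. If fewer TEM patients exit than the document's sm3 rate suggests, the distortion is smaller. The direction of the per-protocol result is therefore not predictable from the document, but the dependence on outcome is built into the rule.

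**What to change.** In the Statistical analysis section, replace the per-protocol definition with one based on treatment received: eligible patients who received the allocated sequence (chemoradiotherapy as specified followed by local excision, or local excision alone) without crossover. State that patients who exit under the listed criteria and have TME remain in the set and count as rectal preservation failures.

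This is one sentence. It changes no clinical rule, no endpoint definition and no sample size, and leaves the ITT analysis as it is. It should be done before any outcome data are seen, because a later redefinition would look data-driven.
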